### Recruitment

Women will be recruited in the following nine European countries: United Kingdom, Ireland, Netherlands, Belgium, Poland, Italy, Spain, Austria, Denmark (2 study centres), from a diverse range of socio-economic and ethnic backgrounds. Participating hospitals, surrounding midwives, obstetricians and general practices are involved in recruitment. Each country will have its own tactics to optimize recruitment (e.g. leaflets, flyers, posters outlining the intervention). An information sheet will be given to all eligible participants, which includes all aspects of the study. Women will have the opportunity to consider participation and to ask questions to the researcher. It is stressed that women can terminate participation at any time within the study without affecting her usual care. The privacy of the participant is protected, and all data will be protected and processed anonymously. Written consent will be obtained prior to the first baseline measurement. Women are requested to give consent for 1) participation in the study, including gathering data, blood sampling, associated measurements and extraction of relevant data from medical records, 2) storage of blood and placenta tissue in a biobank and 3) external examination of their baby at birth. Depending on the site, costs involving study visits, parking or travel expenses will be reimbursed and in some places small gifts for attending the measurement visits will be given. The inclusion period is planned from February 2013 until the end of December 2013, based on recruitment of 2–3 patients a week at each centre. At each site a screening log will contain all patients screened for the study and the reasons why they were not randomised, if this is the case, to allow the consort diagram to be completed.

### Randomisation

Women who are eligible will be randomly allocated to one of the eight intervention arms (as is shown in Figure 
1): 1) healthy eating (HE), 2) physical activity (PA), 3) HE+PA, 4) HE+PA+vitamin D, 5) HE+PA+placebo, 6) vitamin D alone, 7) placebo alone, 8) control. A computerized random number generator draws up an allocation schedule pre-stratified for intervention centre and 2x2 trial. The DALI trial coordinator will prepare sealed opaque envelopes containing the intervention arm to which each participant is allocated. The outcome of the allocation will be reported by the lifestyle coach to the participant, before the start of the intervention. Those involved with measurements are kept blinded of the intervention.

**Figure 1 F1:**
[figure not shown]
**Trial schedule.** * vitamin D arm; PA= Physical Activity; HE= Healthy Eating; Vit D = Vitamin D; GDM= Gestational Diabetes Mellitus; F2F = Face to Face; picture phone = telephone call.

### Procedure

Clinical assessments will be made by a member of the research team at four time points: before 20 weeks (Screening/baseline), 24–28 weeks (visit 2), 35–37 weeks (visit 3) gestation and after delivery. The lifestyle intervention will be delivered by a lifestyle coach (Figure 
1). Vitamin D will be taken daily from randomisation until delivery.

Should GDM develop after baseline, women will be managed according to local standard practice. All treatments will be recorded and the DALI intervention will be discontinued. Measurement procedures, however, will continue, although at 35–37 weeks instead of an oral glucose tolerance test (OGTT) only fasting blood will be collected.

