#### Sample size and power calculation

The primary outcomes of the study are gestational weight gain, fasting glucose and insulin sensitivity in late pregnancy. The numbers needed in each arm (80% power, 5% significance, two tailed alpha) were calculated assuming a 20% drop out. To detect a weight gain difference of 4 kg (mean of 11 kg and standard deviation (SD) of 6.5 kg) we would need 80 women in each arm. To measure a fasting glucose difference of 0.3 mmol/l (mean of 5.0 mmol/l and a SD of 0.5 mmol/l) we would need 85 women in each arm. To find a difference 0.44 for the HOMA-IR (mean of 2.2 and a SD of 0.8) we would need 101 women in each arm. Lesser numbers are required when using the factorial design, combining cells for comparisons. The trial will be conducted in nine European countries (ten study centres) and in each centre 88 women will be recruited (total n = 880) before 20 weeks of pregnancy and randomly assigned to one of the eight arms pre-stratified for centre and 2x2 trial (lifestyle 2x2 or vitamin D/placebo 2x2).

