**Evaluation**						
Dose, reach, fidelity, satisfaction	Questionnaire			x		
Costs^f^, distance, visits	Questionnaire	x	x	x		

^a^ Data collected from routine and expert scans that occur during the time points.

^b^ Blood samples will be collected in the fasting state and at [30, 60, 90 and 120 minutes] or [60, and 120 minutes] depending on site following ingestion of the glucose drink (75 g D-glucose in 250 ml water).

^c^ If GDM is diagnosed by IADPSG criteria, subsequent visits only test the fasting measurements.

^d^ obtained locally only for the vitamin D arm.

^e^ at delivery only registration of adverse events.

^f^ data registration for a longer period post natal.

^g^ collection of samples in a non fasting state.

*PPAQ* pregnancy physical activity questionnaire, *PA* physical activity, *HE* healthy eating, *WHO* world health organisation.

At birth maternal blood is collected shortly before the birth process (or a day after delivery, to minimize disrupting blood levels caused by the delivery itself). Placenta tissue and cord blood is collected and processed within 30 minutes after birth. Neonatal measurements will be performed within 48 hours after birth. The women will be asked to complete a questionnaire and data from the medical records will be requested regarding the delivery.

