### Primary outcome measures

For assessing intervention effects, the primary outcomes are maternal weight gain, fasting glucose levels and insulin sensitivity. Maternal weight gain will be defined as the weight change from baseline measurement to the last measurement at 35–37 weeks of gestation. Insulin sensitivity will be derived from homeostasis model assessment (HOMA)
[75].

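### Late-pregnancy fasting glucose and HOMA are measured after GDM care has begun and the study intervention has stopped, which is expected to bias the glucose difference toward zero

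*Protocol article*

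**What the plan says.** Sample size and power calculation: "The primary outcomes of the study are gestational weight gain, fasting glucose and insulin sensitivity in late pregnancy". Primary outcome measures derives insulin sensitivity from HOMA, that is, from the fasting sample.

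Participants defines GDM by the IADPSG criteria: fasting glucose at or above 5.1 mmol/l, 1 h at or above 10, or 2 h at or above 8.5. Table 1 footnote c applies the same criteria after baseline: "If GDM is diagnosed by IADPSG criteria, subsequent visits only test the fasting measurements".

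Procedure: GDM after baseline is managed by local practice, and then "All treatments will be recorded and the DALI intervention will be discontinued". Measurement continues, with fasting blood only at 35–37 weeks.

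Data analysis: longitudinal multilevel regression by intention to treat, whose coefficient is an average difference between conditions. The article states no exception for values taken after GDM treatment has begun.

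Planning values for glucose: "To measure a fasting glucose difference of 0.3 mmol/l (mean of 5.0 mmol/l and a SD of 0.5 mmol/l) we would need 85 women" per arm, with "80% power, 5% significance, two tailed alpha"; the numbers "were calculated assuming a 20% drop out".

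**The concern.** The event that starts treatment and stops the study intervention is triggered partly by the level of a primary outcome. If the intervention lowers fasting glucose, fewer intervention women reach the threshold, so more controls than intervention women receive glucose-lowering care before the 35–37 week sample. That care lowers the control mean more than the intervention mean. Separately, intervention women who are diagnosed stop the intervention, and some of its effect may fade before they are sampled. Both mechanisms reduce the fasting glucose difference.

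HOMA raises a different problem. If local care includes insulin, which the article does not say, a fasting insulin value taken on it does not reflect the woman's own insulin sensitivity.

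At stake is how a small late-pregnancy difference would be read. It could mean that the intervention had little effect, or that local care brought the control arm down to the same level.

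**Working it through.** **1. The plan's own figure.** n per arm = 2(z_alpha + z_beta)²(SD/difference)². With two-sided 5%, 80% power, SD 0.5 and difference 0.3: 2(1.960 + 0.842)²(0.5/0.3)² = 43.6, so 44, and 44/0.8 = 55. The article gives 85, so its stated inputs do not reproduce its figure. An alpha of 0.05/6 gives 68, and 68/0.8 = 85, but no such alpha is declared. The power figures below use the stated two-sided 5%. Evaluable women per arm: 110 × 0.8 = 88.

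**2. Share reaching the fasting threshold.** P = 1 − Φ((5.1 − mean)/SD). Assumptions: normal values, the fasting criterion alone, and late-pregnancy values applied at 24–28 weeks.

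| Means at 24–28 weeks (SD 0.5) | Control | Intervention | Ratio |
|---|---|---|---|
| 5.0 and 4.7 (full effect) | 1 − Φ(0.2) = 42.1% | 1 − Φ(0.8) = 21.2% | 1.99 |
| 5.0 and 4.85 (half the effect) | 42.1% | 1 − Φ(0.5) = 30.9% | 1.36 |
| 5.3 and 5.0 (5.0 read as the intervention mean) | 65.5% | 42.1% | 1.56 |

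Removing women with baseline fasting glucose of 5.1 or more, as the entry criteria do, lowers both shares and gives ratios of about 2.1 to 2.9 (assumed baseline means 4.6–5.0, correlations 0.3–0.6, full effect).

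**3. Dilution of the difference.** Let t be the drop in fasting glucose from GDM care and L the share of the intervention effect lost after stopping. The article gives neither; both are assumptions.

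Difference = 0.30 − t(p_control − p_int) − L × 0.30 × p_int

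With the full effect at 24–28 weeks, p_control − p_int = 0.209 and 0.30 × p_int = 0.064:

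- t = 0.2, L = 0: 0.30 − 0.042 = 0.258
- t = 0.5, L = 0: 0.30 − 0.104 = 0.196
- t = 0.2, L = 1: 0.258 − 0.064 = 0.195 (before rounding)
- t = 0.5, L = 1: 0.196 − 0.064 = 0.132

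With half the effect at 24–28 weeks there is less imbalance in treatment, but more intervention women stop. For t = 0.3 and L = 1: 0.30 − 0.3 × 0.112 − 0.30 × 0.309 = 0.174, the same as with the full effect (0.30 − 0.063 − 0.064 = 0.174, before rounding).

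**4. Power at two-sided 5%, 88 per arm.** Undiluted: 98%. The last column simulates the two visits as bivariate normal (correlation 0.5–0.7), because treating the highest values also narrows the spread.

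| t | L | Difference | SD held at 0.5 | Simulated spread |
|---|---|---|---|---|
| 0.2 | 0 | 0.258 | 93% | about 95% |
| 0.5 | 0 | 0.196 | 74% | about 80–86% |
| 0.2 | 1 | 0.195 | 73% | about 75% |
| 0.5 | 1 | 0.132 | 42% | about 46–50% |

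With two factorial cells pooled (176 per side) and SD 0.5, power is 96% at t = 0.5, L = 0; 90% at t = 0.3, L = 1; and about 70% at t = 0.5, L = 1 (about 75% with the simulated spread).

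**5. HOMA.** The article gives neither a diagnostic threshold on HOMA nor a treatment effect on it, so no corresponding calculation is possible.

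**The case against.** The strongest reply is that nothing here is contradictory. Continued sampling, recorded treatments and intention to treat together form a legitimate treatment-policy analysis, and a condensed article may leave further handling to an analysis plan. That stands as a reason to keep the as-measured analysis. It does not remove the issue, because the article itself fixes the outcomes, the outcome-triggered stopping and the analysis principle, and these together produce the bias.

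Several stronger readings are tempting, and the documents do not support them:

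- **That twice as many controls are treated on the plan's own figures.** The planning values are for late pregnancy, while the diagnosis that triggers care comes at 24–28 weeks. The article does not say which arm has the mean of 5.0. Lifestyle interventions requires at least four of the five face-to-face sessions before the second measurement, so an early effect is plausible but not established. Reaching 5.1 is also not the same as being treated: Participants notes that not all sites diagnose by the IADPSG criteria.
- **That stopping the intervention affects controls.** Control group says they receive none. Stopping acts only through diagnosed intervention women, and in the lifestyle arms most face-to-face coaching has been delivered by then.
- **That HOMA shrinks as well.** Insulin treatment could raise measured insulin, so the direction is open.
- **That a null result would be uninterpretable.** The longitudinal coefficient also draws on 24–28 week values, and cells are combined when no interaction is found. Both soften the loss.

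**Conclusion.** The concern holds for fasting glucose as an expected bias toward zero. Its direction follows from the article's design if the intervention lowers glucose by 24–28 weeks and local care lowers it further. Its size rests on assumptions: the 0.30 difference becomes about 0.26–0.20 for a treatment drop of 0.2–0.5 mmol/l, and about 0.20–0.13 if the intervention effect is also wholly lost on stopping. Power for two single arms at 5% falls from 98% to about 95–80% in the first case and 75–46% in the second; pooling recovers much of this if there is no interaction. For HOMA the only supported point is that samples taken on exogenous insulin, if there are any, do not measure the intended quantity. This merits a change to the analysis. It does not invalidate the trial, and a late-pregnancy null would be harder to interpret rather than meaningless.

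**What to change.** Change the analysis only:

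1. Keep the as-measured intention-to-treat analysis and say that its effect includes GDM care.
2. Report the between-arm difference at 24–28 weeks as a key secondary result. It precedes treatment of any GDM diagnosed at that visit.
3. Add a supplementary mixed-model analysis that treats fasting glucose and HOMA values after the start of GDM treatment as unobserved. Condition on the 24–28 week fasting, 1 h and 2 h glucose values, since all three define the diagnosis.
4. Do not use HOMA from samples taken on exogenous insulin.

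Treatments are already recorded and sampling already continues, so no new data are needed and no clinical rule changes. The costs are a missing-at-random assumption in the supplementary analysis, the loss of more late values from controls than from intervention women there (42% and 21% on the assumptions above, if all who cross the threshold are treated), and two estimates to report and reconcile.

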### Lifestyle interventions

After randomization, and after receiving all baseline measurement results, the individual sessions with a lifestyle coach will be scheduled for each participant. The coaching is targeted at healthy eating and/or physical activity according to a defined schedule. It builds on principles of patient empowerment and cognitive behavioural techniques, inspired by Motivational Interviewing (MI). Women will be assigned to the same personal coach during the intervention. The overarching intervention framework was derived from a previous lifestyle trial aimed at diabetes prevention in (non-pregnant) adults
[19].

In the programme, one-to-one contact will be offered, along with telephone booster calls. The same amount of time will be offered to every participant during the trial. The intervention will be provided in five sessions of approximately 30–45 minutes duration, and in four optional telephone calls of up to 20 minutes that occur between the one-to-one sessions (see Figure 
1). The one-to-one sessions can take place either in the home of the participants or in the hospital/midwife practice/general practice, depending on local arrangements. The timing of these contacts and the time between these contacts is dependent on the preference of the participant and the availability of the lifestyle coach, in order to deliver the intervention with the most appropriate timing and to optimize chances of the uptake of behaviour change. However it is stressed that at least 4 face-to-face coaching sessions should occur before the second measurement and that the intervention should be finished before 35 weeks of gestation.

To facilitate the coaches and promote treatment integrity, each coach will have a desk-file outlining the intervention and options in detail and will use a Personal Digital Assistant (PDA) to provide a framework for the visit and to help guide the coach to deliver the intervention. The PDA will also be used to record the intervention results / discussion at each step. Details of the session will be entered into the PDA programme as the session progresses or directly at the end of the session in order to focus all attention on the participant. All information will be synchronised to the server of the trial coordination team at the end of each session.

To prepare consultations, answers from the baseline questionnaire on the ‘readiness to change scores’ for all the physical activity and healthy eating messages will be loaded on the PDA and can be used in helping to tailor the intervention, e.g. explain risk factors and identify barriers to change. Participants will choose one or more key items (agenda setting) as their main area of concern: risk factors of GDM, weight management, healthy eating and/or physical activity. The last two can only be chosen once subjects are allocated to these intervention groups.

Once a message has been selected, the first phase of behaviour change is centred on intention formation (motivation). Current behaviour will be assessed and motivation for change will be established. To assess the participants’ readiness to change, coaches can use a ruler for motivation, importance and confidence, prompting the question: “How motivated are you right now to change this specific behaviour on a scale from 1–10, where 1 is not at all motivated, and 10 extremely motivated”. Followed by questions to elicit change talk as “what is the reason you rated yourself at a ‘(for example 4)’ instead of a 1?” and “what do you need to change this 4 to a 6 (number rated as sufficient)?”. These scales are a useful tool for the coach as well as for the participant to gain insight in why change is needed (importance), what is driving the women’s desire to change (motivation) and to increase a person’s own beliefs of own ability to actually make the desired change (confidence). Since an individual’s readiness to change is variable and dynamic, these scales can be used in follow up consultations as well to gain insight in the development of the women’s changes she already experienced and serve as a feedback tool.

To help women resolve feelings of ambivalence and promote intrinsic motivation, perceived disadvantages and advantages of lifestyle change are explored using a decisional balance sheet. The primary focus is on reducing the disadvantages of the current behaviour and promoting the advantage of the preferred behaviour. The status quo will be acknowledged, while ‘change talk’ will be rewarded with positive reinforcement.

If women score low for the importance scale of changing their behaviour, education on risk and benefits might enhance their motivation for change. The communicated risk factors of developing GDM
[20] consist of unchangeable (inherent) risk factors like: previous GDM, family history of diabetes, polycystic ovarian syndrome (PCOS), ethnic background as well as modifiable risk factors like: weight, unhealthy nutrition, insufficient physical activity and excessive sedentary behaviour. The primary focus of the intervention will be on the modifiable factors. The risk communication will serve as an introduction and will build motivation to change their weight, physical activity and nutrition behaviour.

By offering social support, encouraging women to say what could work, talking about past successes and achievements, speculating and exploring extremes, confidence for behaviour change will be enhanced.

Finally, when the woman is ready to make the change, this will be translated into personal goal setting and action planning. Action cards will be used as a tool to help women formulate a specific and realistic goal. Involving questions to alter the chances of success: “What is your action plan?, When will you start?, How will you make this change? What if it did not turn out the way you wanted, what will be your back-up plan?”.

Following realistic goal setting (in subsequent sessions), the women are encouraged and supported in their efforts to eat healthily and/or to be sufficiently physically active. During this action phase, behavioural strategies will be provided along with mobilising social support and identifying and overcoming obstacles where possible.

Participants allocated to one of the five groups with a lifestyle intervention receive a toolkit with useful materials to help them change their behaviour. The content of the toolkit is dependent on the group they are allocated to. All coached participants receive a participant manual, with general information about (risk of developing) GDM, which is explained above, and weight management.

The Institute of Medicine (IOM) has advised on a minimum, mean and maximum weight gain for each pre-pregnancy BMI-group until 40 weeks of gestational age. For the group ≥ BMI 29 it is advised to gain between 5 to 9 kilogram
[21]. While the purpose of the DALI trial is to minimize gestational weight gain, women are advised to gain a maximum of 5 kilogram. If before the start of the intervention, they have already gained ≥ 5 kilogram the advice is to maintain this weight throughout the remaining pregnancy. The goal of the intervention is to make the women aware of the fact that they are able to influence their weight (gain) even during pregnancy. Goal setting to achieve optimal weight gain during pregnancy appears to be helpful
[22]. Therefore, if women find it helpful to keep track of their weight, they have the possibility to measure their weight every session with the lifestyle coach.

Where a lifestyle choice is already in place, fortification discussions will occur. All messages will be reviewed as an option (although they may be promptly discarded). Some of the messages overlap, and so some actions will therefore address more than one message.

#### Physical activity (PA) intervention

According to the American College of Obstetrics and Gynaecology (ACOG) guidelines
[23], pregnant women are recommended to be moderately physically active for at least 30 minutes per day (building up to 60 minutes if possible) on at least 5 days of the week (preferably 7).

Each participant will be advised by attractive messages to:

1. “Be active every day”: Incorporate light and moderate PA as much as possible into their daily life (e.g. by parking further away from destination or undertake special activities for pregnant women).

2. “Sit less”: Reduce sedentary time.

3. “Build your strength”: Incorporate upper and/or lower limb resistance exercise as PA.

4. “Take more steps”: To increase the number of steps taken per day.

5. “Be more active at weekends”: To be more active during the weekends.

An action plan for increasing PA levels will be made during the first session, and evaluated in subsequent sessions. The participants receive a manual with additional information about PA, including an adapted F.I.T.T. model (frequency, intensity, time, type) based on ACOG guidelines
[23] and information about the above mentioned PA advices. To help the women increase their PA they will receive pedometers (Yamax Digiwalker SW-200, Tokyo, Japan) and flexible elastic dynabands (Thera-Band, Akron, USA), respectively to provide feedback about their behaviour and progress and to help them perform at home upper and/or lower limb resistance exercises. For these exercises, an additional (training) video has been developed, containing an 8 min workout with the dynaband and showing specific exercises one by one. The exercises can be found in the manual as well. Included in the manual is also a list with helpful places where pregnant women can go for PA classes, e.g. pregnancy swimming, pregnancy fitness classes and pregnancy yoga. Activities such as swimming, walking and cycling are activities that the participants should be able to undertake during the course of their pregnancy. As pregnancy progresses through the third trimester, PA may decrease and this will be managed sympathetically by providing alternatives e.g. upper limb exercises whilst sitting.

